**Discussion:**

The study received full ethics committee approval. The first patient was enrolled on 27 November 2020. The results of this trial will finally answer the question of whether a nonpressure dressing after open hemorrhoidectomy is necessary and beneficial.

**Trial registration:**

Chinese Clinical Trial Registry ChiCTR2000040283. Registered on 28 November 2020.

## Introduction

### Background and rationale {6a}

As people’s personal and work lifestyles change, the incidence of mixed hemorrhoids in China is increasing annually [1]. According to an epidemiological study, in 2016, the incidence of anorectal diseases among urban residents in China was 51.14%, and the incidence of mixed hemorrhoids was the highest among these diseases, accounting for 50.28% of all anorectal diseases [2]. In the USA, the incidence is approximately 4%, with the prevalence being highest between 45 and 65 years of age [3]. It is estimated that about 50% of Germans have symptomatic hemorrhoids, and some authors believe that up to 70% of people are affected by hemorrhoids [4]. Mixed hemorrhoids can occur at any age, and the symptoms include itching, pain, bleeding, swelling, prolapse of an anal tumor, foreign body sensation, etc. [5]. Although mixed hemorrhoids are not fatal or malignant, these symptoms can reduce a patient’s quality of life and have negative psychological and physical effects [6]. The treatment types include conservative treatment and surgical treatment. Mixed hemorrhoids with mild symptoms can be treated conservatively [7]. However, surgery is the initial treatment of choice in patients with symptomatic grade III–IV hemorrhoids [5, 6, 8]. Various surgical procedures have been used to treat symptomatic hemorrhoids in recent years, but (Milligan-Morgan) ligation is still considered the standard surgical procedure [9–13]. At the end of the operation, the wound is bandaged by a pressure dressing, which is the most traditional type of dressing that has been used clinically for many years [14]. The main purpose of pressure bandaging is to stop bleeding, but it may increase the incidence of postoperative complications, such as urinary retention, pain, anal swelling, and medical adhesive-related skin damage [12, 15–18]. Besides, clinical observation shows that with medical advances and the application of hemostatic drugs, the incidence of active bleeding within 24 h after modified Milligan-Morgan hemorrhoids surgery is very low. In addition, the necessity of pressure dressing after hemorrhoidectomy has received little scientific attention. A previous controlled trial included 67 patients who underwent Milligan-Morgan hemorrhoidectomy [19]. The data indicated that the use of a nonpressure dressing after hemorrhoidectomy reduces the incidence of urinary retention and catheterization. However, the incidence of severe postoperative bleeding and other postoperative complications was not assessed. There is no consensus on whether it is necessary and beneficial to use a nonpressure dressing after hemorrhoidectomy. The results of this randomized clinical study will preliminarily help answer this question.

### Objectives {7}

#### Primary objectives

Incidence of retention of urine within 24 h after operation

#### Secondary objectives

To assess the impact of pressure dressings versus nonpressure dressings surveillance on:
Pain score within 25 h after operation (6H\18H\25H);The change in hemostatic effect scores within 25 h after operation;The incidence of medically adhesive skin lesions;The anal edema score within 25 h after operation (6H\18H\25H);The anal dilatation score within 25 h after operation (6H\18H\25H);Dose of analgesics within 24 h after operation;Hospitalization costs; andLength of stay.

To assess safety, the incidence of adverse events (AEs) and severe adverse events (SAEs) between the two study groups will be compared to illustrate the potential risk to patients with nonpressure dressings after hemorrhoidectomy.

### Trial design {8,9}

This is a single-blind, randomized controlled study that will be conducted in the Department of Integrated Traditional Chinese and Western Medicine at West China Hospital in Sichuan University, China (Fig. 1). Eligible participants who meet the clinical criteria for mixed hemorrhoids of the Professional Committee of Colorectal Diseases, Chinese Society of Integrated Chinese and Western Medicine will be enrolled. The trial was approved by the Ethics Committee on Biomedical Research at West China Hospital of Sichuan University (approval code: NO. 2020-549). It was also registered in the Chinese Clinical Trial Registry (registration ID: ChiCTR2000040283).

**Fig. 1 Fig1:**
[figure not shown]
A flow chart of the study stages

A total of 186 participants with mixed hemorrhoids will be randomly assigned to two groups at a 1:1 ratio. After randomization, the participants in the two groups will undergo surgical treatment with modified Milligan-Morgan hemorrhoidectomy, which only sutured external hemorrhoids to reduce the risk of bleeding under general anesthesia. The incision for external hemorrhoids is fully sutured to stop bleeding. There is no active bleeding after surgery. The experimental group and control group will be treated with nonpressure dressings and pressure dressings, respectively. The timeline for the enrollment process, intervention, and follow-ups is summarized in a SPIRIT figure (Fig. 2). {13}

**Fig. 2 Fig2:**
[figure not shown]
Timeline of the enrollment process, interventions, and assessments. Note: D, discharge; AE, adverse events; NRS, numerical rating scale

### Eligibility criteria {10}

#### Inclusion criteria

The inclusion criteria are as follows:
Grade III–IV mixed hemorrhoids;Aged 18~65 years old;Having the willingness to cooperate during the study;Having provided informed consent; andThe absence of a history of surgery for anorectal diseases. Note: Only the patients who meet the above 5 items will be included in the study.

#### Exclusion criteria

The exclusion criteria are as follows:
Patients with degree IV circular mixed hemorrhoids;Women who are breastfeeding, pregnant, or menstruating;Patients with tuberculosis, diabetes, or cardiovascular, cerebrovascular, liver, kidney, or hematopoietic system disorders;Patients with anorectal inflammation, perianal abscess, tumor, ulcerative colitis, Crohn’s disease, perianal skin disease, or related conditions;Fecal incontinence patients with Wexner score greater than 0 [20]; andPatients in whom the curative effect cannot be determined or who have incomplete data.

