### Recruitment {15}

Researchers will recruit participants from the inpatient wards of Integrated Traditional Chinese and Western Medicine Departments. Patients eligible for the trial must meet all the inclusion criteria and exclusion criteria before enrollment. To recruit enough participants, all doctors in these departments will be informed of the trial and will be asked to contact the research assistant if they encounter potentially eligible patients. Potential participants will be screened, receive information on the trial, and then, be asked to sign informed consent forms. Patients who meet the selection criteria will undergo baseline assessments, and the eligible patients will be asked by medical staff to complete a general information form including their name, sex, age, medical history, etc.

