#### Discontinuations

If participants are unable or unwilling to complete the treatment, or the doctor’s assessment suggests that it is inappropriate to continue the study intervention due to a severe adverse event, we will consider them to be treatment dropouts.

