### Statistical analysis

The validity analysis of the study will be mainly based on intention-to-treat (ITT, all randomized cases) and per-protocol analyses (PP, cases that comply with the trial protocol, good compliance, and completed CRF). First, the Shapiro-Wilk test will be used to test whether the quantitative data follow a normal distribution. If the data are normally distributed, the mean value and standard deviation will be used to describe the quantitative data, and a *t* test will be used for analysis. Nonnormally distributed data will be expressed as the median and quaternary and compared using the Mann-Whitney *U* test. The qualitative data will be expressed as the frequency and percentage; non-grade data will be compared by the chi-square test, and grade data will be compared by the Mann-Whitney *U* test. Randomization will be performed 24 h prior to the surgical intervention. Data will not be collected and analyzed for patients not undergoing surgical intervention. If the scheduled surgery is not performed, the study participant will be excluded from the clinical trial. For every patient who is excluded from the trial after randomization and before the start of the observation period (postoperative wound with or without compression), another study participant will be included to achieve the number of cases needed. The randomization sequence will continue. The next patient will not necessarily be assigned to the same group as the excluded patient. This research will continue until the required number of evaluable patients is reached. Due to complications, a very small number of patients may not be able to comply with the randomly assigned treatment. The study will not exclude these patients. All statistical tests will be two-sided, and *P* < 0.05 will be considered statistically significant. If baseline factors are inconsistent between the two groups, subgroup analysis and multivariate analysis will be considered.

In the safety analysis, Fisher’s exact test will be used to compare the incidence of AEs and SAEs by category (severity) between the two groups.

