## Discussion

Pressure dressings are commonly used and have been considered a clinical standard for wounds after mixed hemorrhoid operations in China. However, these dressings can lead to some postoperative complications, and there are few reports on improvements in wound dressing methods after hemorrhoid surgery. This study will be carried out to determine whether nonpressure bandaging can be used routinely after open hemorrhoidectomy and whether it may be considered in specific circumstances.

During the operation, the patients will be treated with general anesthesia, and the method of applying a pressure dressing is complicated, so at least two medical staff will perform wound bandaging; nonpressure dressings need only a self-adhesive foam dressing, and only one medical staff member will be needed to perform wound dressing, and the process takes less time. The nonpressure dressing method can not only reduce the workload of medical staff but also save time.

Methods to minimize bias were implemented whenever possible. Randomization was performed 24 h before surgery. Randomization ensures a statistically consistent baseline between the experimental and control groups. However, one limitation of this study is that the researchers and patients cannot be blinded to the group assignments. The blinding of patients is an important way to prevent bias, but unfortunately, this step cannot be carried out in this study. However, the observers can be blinded. Before conducting any trial-related procedures, the researcher will obtain a written informed consent from each potential research participant. Randomization will be performed with a random number table generated in Excel, and then, the patients will be assigned a group according to the order of admission.

The research plan is consistent with clinical practice to the greatest extent possible to ensure complete and trouble-free data collection. Observation indicators such as pain and anal swelling may have affected the evaluation at certain time points while the patient is sleeping. Missing data are expected in these cases, but they should be minimized. The research leader will bear full legal responsibility for the entire study and publish the data on the website of the Clinical Research Management Department of West China Hospital of Sichuan University. Anyone who needs data can contact the author.

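### Two exclusion rules contradict the stated intention-to-treat set of all randomized cases, and one of them depends on information that exists only after treatment

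*Protocol article*

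**What the plan says.** All references are to the protocol article.

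- **Statistical analysis** states that the analysis is "mainly based on intention-to-treat (ITT, all randomized cases) and per-protocol analyses". The per-protocol set is defined as "cases that comply with the trial protocol, good compliance, and completed CRF".
- **Exclusion criteria**, last item, removes patients "in whom the curative effect cannot be determined or who have incomplete data".
- **Recruitment {15}** says that eligible patients "must meet all the inclusion criteria and exclusion criteria before enrollment".
- **Statistical analysis** also places randomization 24 h before surgery and then says: "Data will not be collected and analyzed for patients not undergoing surgical intervention". Those patients leave the trial and are replaced, and recruitment runs on until the required number of evaluable patients is reached. Replacement is limited to exclusions before the observation period starts.
- The same section keeps patients who, because of complications, cannot follow their assigned treatment.
- **Discontinuations** covers patients who cannot or will not complete treatment, or whose doctor judges it inappropriate to continue "due to a severe adverse event, we will consider them to be treatment dropouts".

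**The concern.** A set of all randomized cases cannot stand beside rules that take randomized patients out and record nothing on them. A reader cannot tell from the text who enters the comparison of urinary retention.

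The two rules differ in weight. The last exclusion criterion is the serious one, because its first half turns on how treatment went. If it is used after randomization, who remains can depend on outcome and on arm, and the protection that randomization gives is lost. Completeness of the case report form is already a condition of the per-protocol set. Applying a completeness condition to the intention-to-treat set as well pulls the two sets together, so they no longer check each other.

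The no-surgery rule acts before the dressing, so there is no outcome to select on. It biases only if cancellation depends on allocation. Allocation is already fixed up to 24 h earlier, and under Randomization and blinding the primary investigator holds and opens the envelopes, so independence is plausible but not guaranteed.

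**Working it through.** **Step 1: the passages side by side.**

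| Rule | When it can be applied | Compatible with all randomized cases? |
|---|---|---|
| Curative effect cannot be determined | Only after surgery and dressing | No |
| Incomplete data | At screening, if baseline data are meant; otherwise after treatment | Only on the baseline reading |
| No surgery: excluded, replaced, no data | Between randomization and surgery | No; this is a modified set |
| Non-compliance due to complications: kept | After surgery | Yes |
| Treatment dropout (Discontinuations) | After dressing starts | Yes; the text does not remove them from analysis |

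The first and third rows are the contradiction. Neither depends on an analysis plan that is not shown.

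**Step 2: the plan's own sample size.** Inputs from Sample size {14}: 44.7% and 24.7%, two-sided 0.05, power 80%, ratio 1:1, dropout 10%, 186 in total. With unpooled variance:

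n = (1.960 + 0.842)² × (0.447×0.553 + 0.247×0.753) / 0.20² = 85 per arm.

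Dividing by 0.9 gives 95 per arm (190 in total); multiplying by 1.1 gives 94 (188 in total). Both lie within 3% of 186. The pooled formula gives 88 per arm, or 196 in total after division by 0.9. The point here does not rest on this figure; it only confirms the rates and the dropout allowance as usable inputs.

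**Step 3: how far selective removal could move the result.** The number of exclusions is not stated. Assumption: 93 randomized per arm, true rates as in Sample size, and 9 per arm removed (93 × 0.10 = 9.3). The size of the difference does not depend on which arm carries which rate.

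- Expected events: 93 × 0.447 = 41.6 and 93 × 0.247 = 23.0.
- Higher-rate arm: remove 9 events, (41.6 − 9)/84 = 38.8%; remove 9 non-events, 41.6/84 = 49.5%.
- Lower-rate arm: remove 9 events, (23.0 − 9)/84 = 16.6%; remove 9 non-events, 23.0/84 = 27.3%.
- Smallest difference: 38.8 − 27.3, about 11.4 points (11.5 from the rounded rates). Largest: 49.5 − 16.6 = 32.9 points.

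With 5 per arm removed (88 left), the same steps give 41.6% to 47.2% and 20.4% to 26.1%, so about 15.5 to 26.8 points.

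**Step 4: the reverse question.** Suppose the 84 retained per arm show the design rates: 38/84 against 21/84, a difference of 20.2 points, p = 0.006 (chi-square without continuity correction). Putting the 9 per arm back in the most extreme ways gives 38/93 against 30/93 = 8.6 points (p = 0.22), up to 47/93 against 21/93 = 28.0 points (p < 0.001). Steps 3 and 4 answer different questions, so their ranges need not agree. Both show that at this level of loss the choice of set could change the conclusion in the extreme case.

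**The case against.** The strongest reply is that the last exclusion criterion is loose drafting. It sits in a list that Recruitment says is settled before enrollment, and nothing in Statistical analysis applies it after treatment. That reading works for incomplete data, which may mean missing baseline information. It does not work for an effect that cannot be determined, because no effect exists at screening. The clause therefore still needs correction.

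It is also fair that patients without surgery have no postoperative outcome, that replacement stops before the observation period, and that observers and statisticians are blinded (Randomization and blinding), even though patients and researchers are not (Discussion). This makes the no-surgery rule mainly a matter of naming and reporting.

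Three stronger readings may tempt a reader, and the article does not support them.

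- **One missed score while asleep removes a patient from the whole trial.** Of pain and swelling scores at such times, the Discussion says "Missing data are expected in these cases, but they should be minimized". That describes missing values and states no exclusion.
- **Patients stopped for a severe adverse event leave the analysis, so bleeders disappear.** Discontinuations calls them treatment dropouts and says nothing about analysis. It is compatible with keeping patients who cannot comply because of complications, and bleeding that needs surgical revision is itself a score on the hemostatic scale.
- **The 11 to 33 point range is what to expect.** It assumes that the whole dropout allowance is removed under these rules, with events taken from one arm and non-events from the other. Nothing in the article says that this will happen.

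**Conclusion.** The contradiction stands, in two parts. The clause on undeterminable effect or incomplete data cannot be met before enrollment as worded; used later, it would make the primary set depend on post-treatment information. The no-surgery rule makes the set a modified intention-to-treat set, with bias only if cancellation depends on allocation.

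No expected bias can be computed, because the article gives no number of exclusions. The illustrative worst case is an apparent difference of about 11 to 33 points for a true 20 points, with 9 of 93 removed per arm (about 15 to 27 points with 5 of 93). This should be fixed before analysis. It is a defect in how the set is defined, not evidence that the results will be biased.

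**What to change.** 1. Delete the last exclusion criterion, or limit it to baseline information available before randomization.
2. Define one primary set and name it correctly. Either take all randomized patients, analysed as assigned, and drop the rule that no data are collected without surgery; or take all randomized patients who had surgery, analysed as assigned, and call it modified intention-to-treat.
3. Report every post-randomization exclusion by arm with its reason, including cancelled operations. Replacement can continue, provided that replaced patients are counted in the flow of participants.
4. State that urinary retention and re-operation are counted from the chart for every patient in that set, including those recorded as treatment dropouts, whatever secondary scores are missing.

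The cost is an amendment to the wording and a log of cancellations by arm. The sample size does not change. Retention is an inpatient outcome within 24 h, so little further data collection is needed.

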### Sample size {14}

The results of this study will be compared with the two-sided, two-sample chi-square test. The sample size should provide 80% statistical power at a significance level of 0.05, and a sample size ratio of 1:1. In the preliminary trial, the incidence of urinary retention was the main outcome measure and was 44.7% in the nonpressure dressing group and 24.7% in the pressure dressing group. Considering an anticipated dropout rate of 10%, we plan to include a total of 186 participants, with 93 participants per group.

### Study setting {9}

This trial will take place at the department of integrated traditional Chinese and Western medicine, West China Hospital, Sichuan University, China.

### Recruitment {15}

Researchers will recruit participants from the inpatient wards of Integrated Traditional Chinese and Western Medicine Departments. Patients eligible for the trial must meet all the inclusion criteria and exclusion criteria before enrollment. To recruit enough participants, all doctors in these departments will be informed of the trial and will be asked to contact the research assistant if they encounter potentially eligible patients. Potential participants will be screened, receive information on the trial, and then, be asked to sign informed consent forms. Patients who meet the selection criteria will undergo baseline assessments, and the eligible patients will be asked by medical staff to complete a general information form including their name, sex, age, medical history, etc.

## Randomization and blinding

Randomization will be performed by an independent statistician with no clinical involvement in this trial by use of a random number generator program in Excel software (Kingsoft Office Software Co. Ltd., China). A simple randomization method and table of random numbers will be used. If the selected number is even, the patient is allocated to the nonpressure dressings group, and if it is odd, the patient is allocated to the pressure dressings group in a 1:1 ratio. Only one data administrator can access the random number table on the computer. An independent staff member who will not take part in the performance of this study will seal the random numbers in opaque envelopes. Then, the primary investigator will save these envelopes and open one of them when a participant is enrolled.

The participants will be enrolled by nursing staff and research assistants in the order of admission time. And they will be grouped by the data administrator using the table of random numbers. The two groups will use different types of dressings, and the operators will place the dressings. The patients can feel whether the wound is pressurized, so they cannot be blinded. However, the operators will remove the dressing before the observer’s follow-up. The observers and statisticians will be blinded to the group assignments.

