**Methods:**

In this study, we plan to include 186 patients who have undergone modified Milligan-Morgan hemorrhoidectomy, which only sutured external hemorrhoids to reduce the risk of bleeding. The purpose is to determine whether the use of nonpressure dressings after open hemorrhoidectomy is inferior to the use of pressure dressings in terms of severe postoperative bleeding and postoperative complications. The primary endpoints of the trial are the incidence of urinary retention within 24 h after surgery and the incidence of severe postoperative bleeding 1 h after dressing removal, which requires revision surgery within 24 h after the surgery. The secondary endpoints of the study are the pain score, anal distension score, postoperative use of analgesics, and incidence of medical adhesive-related skin injury, all of which will be assessed before removing the dressings. The length of hospitalization in days and hospitalization expenses will be recorded. Safety will be assessed with consideration of all adverse and severe adverse events related to the study treatment.

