### Ancillary and post-trial care {30}

All participants will return to usual care after dressing removal at postoperative 24 h. As part of our safety protocol, we will monitor patients’ surgical wound pain, micturition, skin damage, and active bleeding. Any participants with the above abnormal situations will be contacted by the site coordinator who will inform the doctor for timely treatment.

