#### Secondary outcome measures

Postoperative pain will be measured at rest with routine care at 6, 18, and 25 h by using a visual analog scale (VAS) after the surgical procedure. The scale will range from 0 to 10 points, with higher scores indicating more severe pain [21]: 0 = no pain, 1~3 = slight pain that can be tolerated, 4~6 = pain that can be tolerated but affects sleep, and 7~10 = unbearable pain that affects not only appetite but also sleep.The change in hemostatic effect scores within 25 h will be the other primary outcome. The effect of hemostasis will be graded using a 3-point ordinal scale: 0 = the dressing was not soaked before removal, 1 = there was no bleeding after changing the dressing due to excessive blood oozing, and 2 = postoperative bleeding requiring surgical revision occurred.The change in mean rectal tenesmus sensation scores within 25 h will be graded using a 3-point ordinal scale: 0 = no abnormal sensation; 1 = mild anal discomfort, occasionally abnormal sensation; 2 = strong foreign-body sensation; and 3 = strong foreign body sensation that is not easily relieved after rest or treatment.The incidence of medical adhesive-related skin injuries will be measured. The skin condition will be assessed by a senior wound specialist nurse. If there is no skin damage, “no” will be recorded. When any of the following situations occur, “yes” will be recorded: (1) exfoliation, (2) tension blisters, (3) skin lacerations, (4) contact dermatitis, and (5) allergic dermatitis. In the statistical analysis, the incidence of medical adhesive-related skin damage will be calculated by a statistician.The change in the mean anal edema score when the dressing is removed 24 h after surgery will be graded using a 4-point ordinal scale: 0 = no anal edema, 1 = mild edema (< 1/4 anal area ), 2 = moderate edema (1/4 to 1/2 anal area ), and 3 = severe edema (> 1/2 anal area ).The total dose of analgesics before removing the dressing will be recorded.The length of hospitalization will be recorded in days.Hospitalization expenses will be recorded.

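### Observer blinding rests on removing the dressing first, but removal is at 24 h, so it cannot cover urinary retention or the 6 h and 18 h scores; the stated assessment times also conflict

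*Protocol article*

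**What the plan says.** Under Randomization and blinding, the article concedes that patients feel the pressure and so cannot be blinded. It then gives the means of blinding the observers, "the operators will remove the dressing before the observer’s follow-up", and concludes: "The observers and statisticians will be blinded to the group assignments". The Discussion repeats that patients and researchers cannot be blinded but observers can. Trial design calls the study single-blind.

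The time of removal is in Ancillary and post-trial care: "All participants will return to usual care after dressing removal at postoperative 24 h".

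The assessment times are stated in several places:

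- Primary objectives and Primary outcome measures count urinary retention over the first 24 h. It is defined by failure to void despite a hot compress or drugs, ending in catheterization.
- Secondary outcome measures: "Postoperative pain will be measured at rest with routine care at 6, 18, and 25 h". Secondary objectives gives the same three times for pain and for anal dilatation.
- The abstract's Methods lists pain, distension, analgesic use and adhesive-related skin injury, and adds: "all of which will be assessed before removing the dressings".
- Edema has two schedules. Secondary objectives has "The anal edema score within 25 h after operation (6H\18H\25H"; Secondary outcome measures has "The change in the mean anal edema score when the dressing is removed 24 h after surgery".
- The abstract assesses severe bleeding one hour after the dressing comes off, but requires the revision surgery to fall within 24 h of the operation.

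**The concern.** The blinding claim has no limit, but its justification has one: it works only for what an observer sees after the dressing is gone. The two dressings look different. One is a built-up gauze compress held by two long tapes running from the groin to the back; the other is gauze under an adhesive foam dressing (Intervention description). Anyone who sees the patient's dressing can tell the arm.

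At stake is how the main result will be read. Retention is counted when it ends in catheterization, a ward decision taken while the dressing is on. A reader who accepts the blinding sentence would take this outcome to be protected against detection bias, and nothing in the article provides that protection. The conflicting times add a second difficulty: for several outcomes the article does not settle whether a rating belongs to the dressing-on or the dressing-off period, so it is also unclear whether the mechanism could apply to it.

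**Working it through.** There is no statistical figure to reproduce. The check sets each stated assessment time against the stated removal time of 24 h.

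| Outcome | Stated time | Position relative to removal | Can removal first blind the observer? |
|---|---|---|---|
| Urinary retention | 0 to 24 h | Whole window with dressing on | No |
| Pain, 6 h and 18 h | 6 < 24; 18 < 24 | Before | No |
| Anal dilatation (distension), 6 h and 18 h | 6 < 24; 18 < 24 | Before | No |
| Pain and distension, 25 h | 25 = 24 + 1 | After | The observer yes, but the score is the patient's own |
| Edema, Secondary outcome measures | At removal, 24 h | At removal | Yes, if rated once the dressing is off by someone who did not see it |
| Edema, Secondary objectives | 6, 18 and 25 h | Two before, one after | Only at 25 h |
| Skin injury | Abstract: before removal; Secondary outcome measures: no time | Unclear | Yes, if inspected after removal |

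So 2 of the 3 scheduled score times, and all of the 24 h retention window, lie outside the reach of the mechanism.

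The times that do not agree are these:

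1. **Pain and distension.** The abstract puts them before removal. Secondary objectives schedules both at 25 h, Secondary outcome measures has the same time for pain, and 25 h is one hour after removal. The abstract's wording also conflicts with the blinding mechanism: if those outcomes are assessed before the dressing comes off, removal does not precede the observer's assessment of them.
2. **Edema.** One section has three times, the other a single rating at 24 h.
3. **Severe bleeding.** One hour after removal is 24 + 1 = 25 h, which lies outside the 24 h within which the revision surgery must fall.

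**The case against.** The fair case on the other side is that the open-label character of the trial is largely disclosed. The article says that patients cannot be blinded, names this as a limitation together with the lack of blinding of researchers, and never claims that the staff who decide on catheterization are blinded. The mechanism is coherent for ratings made after removal, and the claim about statisticians is not affected. Pain is scored on a visual analog scale, which does not require looking at the wound. All of this stands. It narrows the fault to an unqualified sentence about observers and to the conflicting times; it does not make that sentence true for retention or the early scores.

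Four stronger readings are tempting and are not supported:

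- **That every observer knew the arm.** The article does not say who records retention or the 6 h and 18 h scores. It shows only that the stated means cannot blind them.
- **That the 25 h scores are pooled with the earlier ones and dilute the effect.** No section averages or pools the time points.
- **That most secondary outcomes are unprotected.** Of the eight in Secondary objectives, length of stay and cost are administrative records, and edema and skin injury can be rated after removal.
- **That the bias has a known size.** The documents contain nothing from which an amount could be derived.

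**Conclusion.** The point holds in this form: the blinding statement is wrong as written for the primary outcome of retention and for the 6 h and 18 h scores, and three sets of assessment times contradict each other. In extent, it affects the whole retention window and two of three score times. The possible bias in the result cannot be quantified from the article.

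At 25 h the gain is also limited. Pain and distension are still reported by patients who know which dressing they had, so a blinded observer does not turn them into blinded outcomes.

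The conclusion assumes that the 24 h removal time applies to all patients, as the article states, and that removal before follow-up is the only blinding measure, since no other is described.

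**What to change.** - In Randomization and blinding and in the Discussion, limit observer blinding to observer-rated outcomes assessed after removal, such as edema or skin inspection.
- State that retention and the 6 h and 18 h scores are open-label, and that pain and distension at every time point, including 25 h, are reported by unblinded patients.
- Report the 25 h scores as post-removal, separately from the dressing-on scores at 6 h and 18 h.
- Reconcile the times for edema, for pain and distension, and for severe bleeding across the abstract, Secondary objectives and Secondary outcome measures. The documents do not show which version was intended, so the investigators must settle each one.
- Record the time of and reason for each catheterization on the case report form, so that differences between the arms in how the decision was reached can be examined.

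Most of this is wording. The price is a weaker, but true, blinding statement. Recruitment was under way (Trial status), so the new fields would cover only patients not yet treated, and the article requires modifications to go to the ethics committee for review.
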